#### Sample size

Sample size calculations were performed for each of the ACLF and hepatic decompensation arms using a 2-sided alpha of 5%, a power of 80%, and an anticipated 20% dropout.

For the ACLF cohort, we used the primary endpoint 28-day mortality, based on published rates of 22–74%, with a rate of 33.9% demonstrated in a study of 1343 hospitalised patients at 29 liver units in 8 European countries [2]. A 75% reduction in mortality in the intervention group generates a mortality rate of 8.5%, a conservative estimate considering our feasibility study of 59 participants resulted in a 3% 28-day mortality rate. We calculate a total sample size of 120 participants or 60 in each arm for the ACLF cohort. For the hepatic decompensation cohort, the sample size calculation is based on the primary endpoint of 30-day re-admission, which is estimated 17–38% [3, 29, 30]. Re-admission rates in our feasibility were 50% lower than anticipated at 18% by 30-days therefore we used an anticipated 17% 30-day re-admission rate in the intervention arm. We calculate a total sample size of 320 or 160 in each arm for the hepatic decompensation cohort. . Sample size calculation was performed using Stata statistical software, version 16.1 for Mac (StataCorp, College Station, TX, USA).

#### Statistical analyses

The data analysis for the primary composite endpoint of death, referral for liver transplantation or 30-day readmission from the date of hospital discharge will be undertaken on an intention-to-treat basis. A 28-day mortality rate will be calculated from the date of randomisation. For the primary and other binary outcomes, chi-squared tests will be used to compare the intervention and control groups. Survival analyses will also be undertaken, with the generation of Kaplan-Meier curves and Cox regression analyses to derive (adjusted) hazard ratios. For continuous outcomes, t-tests or non-parametric equivalents (e.g., Mann-Whitney tests) will be applied to compare the intervention and comparator groups. A *p* value of 0.05 is considered significant and 95% confidence intervals will be reported for all effect estimates Three exploratory subgroup analyses are planned: (a) comparing groups by the source of referral—conducted to address bias created following randomisation whereby in-patients in the intervention arm may be discharged home earlier due to perceived safety with regular home visits compared to those in the control arm. This subgroup analysis will account for differences between those admitted from in-patient admission compared to the emergency department or the ambulatory liver clinic; (b) comparing groups by re-enrolment to LivR Well after drop out due to unplanned re-admission to hospital. Data from the first enrolment to LivR Well will be included in the primary outcomes on an intention-to-treat basis and (c) patients with COVID-19 at the time of referral. Analyses will be performed using Stata statistical software, version 16.1 for Mac (StataCorp, College Station, TX, USA).

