**Methods:**

We will recruit adult patients with chronic liver disease from the emergency departments, in-patient admissions, and an ambulatory liver clinic of a multi-site quaternary health service in Melbourne, Australia. A total of 120 patients meeting EF-Clif criteria will be recruited to the ACLF arm, and 320 patients to the hepatic decompensation arm. Participants in each cohort will be randomised to the intervention arm, a 28-day multidisciplinary programme or to standard ambulatory care in a 1:1 ratio. The intervention arm includes access to nursing, pharmacy, physiotherapy, dietetics, social work, and neuropsychiatry clinicians. For the ACLF cohort, the primary outcome is 28-day mortality. For the hepatic decompensation cohort, the primary outcome is 30-day re-admission. Secondary outcomes assess changes in liver disease severity and quality of life. An interim analysis will be performed at 50% recruitment to consider early cessation of the trial if the intervention is superior to the control, as suggested in our feasibility study. A cost-effectiveness analysis will be performed. Patients will be followed up for 12 weeks from randomisation. Three exploratory subgroup analyses will be conducted by (a) source of referral, (b) unplanned hospitalisation, and (c) concurrent COVID-19. The trial has been registered with the Australian New Zealand Clinical Trials Registry.

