#### Outcomes

##### Primary outcomes

ACLF cohort: 28-day mortalityHepatic decompensation cohort: 30-day re-admission

Secondary outcomesChanges in liver disease severity using Model for End-stage Liver Disease Score and Child-Pugh class assessed at day 28 and week 12 compared to baselineQuality of life using Chronic Liver Disease Questionnaire and EQ-5D at week 6 compared to baselineCost-effectiveness compared to standard care.

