We acknowledge limitations in this study design and the ways we have attempted to address these. The trial is unblinded by nature, which may influence decisions such as referral for liver transplantation, re-admission to and discharge from hospital, clinical decisions especially for the control group, and referral for other procedures eg elective surgery. The statewide liver transplantation unit is external to Monash Health therefore referrals for consideration of transplantation are made using the centre’s own criteria. The other decisions will be challenging to address the influence of knowledge of the allocation group, and as such we will include this in the discussion. Patients in the intervention group may be re-admitted to the hospital faster due to close follow up or conversely, patients in the control group may be re-admitted at a lower threshold due to the absence of home-based support.

The economic evaluation will be a cost-effectiveness analysis and is essential to guide health services to strategically invest in sustainable ambulatory care to reduce emergency presentations and improve healthcare-related quality of life. This is of particular importance in this population with a high healthcare system burden [33], re-admission [34], and mortality rates.

The subgroup analyses are considered ‘exploratory’ as we acknowledge the potential for bias and challenging interpretation of results. It is unlikely with our total sample sizes that the subgroups will be adequately powered to draw conclusions and therefore another consideration could be using these data in a sensitivity analysis.

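### The Statistical analyses section names a composite as primary, contradicting the two cohort-specific primaries on which the trial is defined and sized

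*Protocol article*

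**What the plan says.** Three sections of the protocol article agree. The abstract states: "For the ACLF cohort, the primary outcome is 28-day mortality", and "For the hepatic decompensation cohort, the primary outcome is 30-day re-admission". The Primary outcomes list reads "ACLF cohort: 28-day mortalityHepatic decompensation cohort: 30-day re-admission". The Sample size section uses 28-day mortality for the ACLF cohort, and for the decompensation cohort "the sample size calculation is based on the primary endpoint of 30-day re-admission".

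The Statistical analyses section departs from this. Its first sentence commits the intention-to-treat analysis to a "primary composite endpoint of death, referral for liver transplantation or 30-day readmission from the date of hospital discharge". The next sentence says "A 28-day mortality rate will be calculated from the date of randomisation", without calling that rate primary. Then comes the test: "For the primary and other binary outcomes, chi-squared tests will be used to compare the intervention and control groups".

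No other section defines a composite. Transplant referral is neither a primary nor a secondary outcome in the Outcomes section; it appears only as an item under Data collection. The Discussion acknowledges that the trial is unblinded, "which may influence decisions such as referral for liver transplantation".

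**The concern.** A reader who follows the Outcomes section and one who follows the Statistical analyses section would test different variables under the name of primary outcome. The article gives no rule for which prevails. If the analysis sentence is followed as written, the headline test is of an endpoint on which neither cohort was sized. If it is left unresolved, a choice remains that could be made, or appear to have been made, after results are known.

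The composite has two further weaknesses. One component, referral for transplantation, is a decision by clinicians who know the allocation; a difference between arms in referral would count as a difference in failure, whatever caused it. And the composite's clock starts at hospital discharge, which not every recruited patient has.

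**Working it through.** **1. Is the trial sized on the single endpoints?**

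Inputs from Sample size: two-sided alpha 5%, power 80%, dropout 20%; ACLF 33.9% against 8.5%, stated total 120; decompensation 17% in the intervention arm, control rate not stated (only a range of 17–38%), stated total 320.

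Formula per arm, with p̄ the mean of the two rates and d their difference:
n = [1.96·√(2p̄(1−p̄)) + 0.842·√(p₁(1−p₁) + p₂(1−p₂))]² / d².
Continuity-corrected: n′ = (n/4)·[1 + √(1 + 4/(n·d))]². Dropout: divide by 0.8.

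| Cohort | Rates | Correction | Evaluable per arm | After dropout | Total | Stated |
|---|---|---|---|---|---|---|
| ACLF | 33.9% v 8.5% | no | 40 | 50 | 100 | 120 |
| ACLF | 33.9% v 8.5% | yes | 47 | 59 | 118 | 120 |
| Decompensation | 32% (assumed) v 17% | no | 128 | 160 | 320 | 320 |
| Decompensation | 33% (assumed) v 17% | yes | 126 | 158 | 316 | 320 |

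The ACLF figure is reproduced to within rounding from mortality alone. The decompensation figure is consistent with re-admission alone at a control rate of about 32–33%, which is back-solved here and not stated in the article. No composite rate enters either calculation.

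**2. What would the composite do to power?**

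The documents give no composite rates, so this is illustration only. Assume independent components, so that each arm's composite risk is 1 − Π(1 − component risk), and use the uncorrected two-proportion test with 128 evaluable per arm (160 × 0.8) for decompensation and 48 (60 × 0.8) for ACLF.

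Decompensation, re-admission 32% v 17%, adding components (control v LivR Well):

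| Added | Composite | Power |
|---|---|---|
| nothing | 32.0% v 17.0% | 80% |
| referral 5% v 5% | 35.4% v 21.2% | 72% |
| referral 5% v 10% | 35.4% v 25.3% | 42% |
| referral 10% v 20% | 38.8% v 33.6% | 14% |
| death 10% v 5% | 38.8% v 21.2% | 87% |
| death 10% v 5% and referral 5% v 5% | 41.9% v 25.1% | 82% |
| death 10% v 5% and referral 5% v 10% | 41.9% v 29.0% | 57% |

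ACLF, death 33.9% v 8.5%, adding re-admission:

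| Added | Composite | Power |
|---|---|---|
| nothing | 33.9% v 8.5% | 87% |
| re-admission 34.4% v 34.4% | 56.6% v 40.0% | 37% |
| re-admission 34.4% v 17% | 56.6% v 24.1% | 91% |

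The 34.4% is the health service's own ACLF re-admission rate given in the Background, and the 17% is borrowed from the decompensation assumption. All death and referral rates added in the decompensation table are assumptions. Power moves in both directions.

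**3. Time origin.** The composite counts from hospital discharge, the mortality rate from randomisation. The Recruitment section takes patients after an acute admission, directly from the emergency department, or from the complex care liver clinic when ACLF or decompensation develops. A patient recruited from clinic may have no discharge from which to count. The composite sentence also gives no time window for death or referral.

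**The case against.** Three sections agree on the primaries and only one sentence departs from them, so the composite may be a leftover from another version of the plan. The Screening and randomisation section also says that primary outcome ascertainment and the data analyses will be blinded. That lowers the risk of selective reporting. It does not say which variable is primary, and the dissenting sentence sits in the section that governs the analysis.

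On referral, the Discussion offers a mitigation: the transplant unit is external and referrals use that centre's own criteria. This is a partial answer and deserves credit; the decision to refer still rests with clinicians who know the allocation. The same Discussion sentence lists re-admission as equally open to influence, so the weakness is not peculiar to referral and does not by itself disqualify the composite. Nor do the documents show that LivR Well would raise referrals: controls also attend a clinic led by a gastroenterologist.

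A reader might infer that the composite costs the trial power. The documents do not support this. The scenarios showing a loss either add referral at an equal or higher rate in LivR Well and leave out any benefit on death, or give ACLF re-admission no treatment effect; other equally arbitrary assumptions raise power. A reader might also take 32% v 17% as the authors' own assumption. It is one back-solved pair, and 33% with continuity correction fits nearly as well.

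**Conclusion.** The contradiction stands. The Statistical analyses section names a primary endpoint that differs from the one in the abstract, the Primary outcomes list and the Sample size section, and nothing in the article reconciles them. Following that section as written would test an endpoint on which neither cohort was sized.

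The consequence for power is unknown in size and direction. In the illustrations it runs from 14% to 87% in the decompensation cohort (80% for re-admission alone) and from 37% to 91% in the ACLF cohort (87% for mortality alone). These ranges rest on independent components and assumed rates; they show only that the result can depend heavily on which endpoint is called primary. The susceptibility of referral to knowledge of allocation, and the discharge-based clock, are secondary weaknesses of the composite.

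This must be fixed before analysis, because the primary endpoint is wrong or ambiguous as written.

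**What to change.** Rewrite the opening sentences of Statistical analyses so that the primaries are those in the Primary outcomes list: death by day 28 from randomisation for the ACLF cohort, and re-admission within 30 days for the decompensation cohort. Give each one stated time origin that exists for every recruitment source, including clinic. Label the composite as secondary, with a window for each component, or delete it. Report transplant referral separately by arm.

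Re-admission alone counts a patient who dies before re-admission as event-free. This can be handled by a supportive analysis of re-admission or death within 30 days. Making that the primary would introduce another endpoint on which the trial was not sized.

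If the composite is truly intended as primary, change the abstract, Primary outcomes and Sample size sections to match, say to which cohort it applies, and restate sample size and power on stated composite rates.

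The first route costs only wording: the sizes of 120 and 320 stay as they are, and no new data are needed, since deaths, admissions and referrals are already collected. The second route requires a new sample size calculation.

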#### Screening and randomisation

Patients will be screened against inclusion and exclusion criteria at the time of diagnosis of ACLF or hepatic decompensation. Those who meet the criteria will be enrolled into the study and provided informed consent. These recruited patients will be randomised in a 1:1 ratio to either the LivR Well programme or to complex care liver clinic in the control arm. Participants will be computer randomised and informed of their allocation by the CLD nurse specialist prior to discharge or within 24 hours of obtaining informed consent. Patients from both study arms will be registered on the Virtual Hospital masterlog through the Microsoft Power Apps program. Due to the nature of the intervention, blinding of study participants or clinical staff administering the LivR Well programme will not be possible. However, outcome ascertainment for the primary outcome, as well as the health services utilisation secondary outcomes will be blinded. Furthermore, all data analyses will be undertaken in a blinded manner. The statistician will be blinded to the feasibility study data results and the treatment allocation of the RCT.

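### Continuous secondary outcomes are tested without the baseline covariate, which costs precision; in the ACLF cohort the place of deaths in these scores should also be fixed in advance

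*Protocol article*

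**What the plan says.** The Outcomes section lists MELD and Child-Pugh class at day 28 and week 12, and CLDQ and EQ-5D at week 6, each set against baseline. Table 5 schedules blood tests, EQ-5D and CLDQ at day 1, so baseline values will exist.

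The Statistical analyses section then fixes the tests. For scores: "For continuous outcomes, t-tests or non-parametric equivalents (e.g., Mann-Whitney tests) will be applied to compare the intervention and comparator groups". For the primary and other binary outcomes: "chi-squared tests will be used to compare the intervention and control groups". Neither sentence names a covariate. The same section adds Cox models with hazard ratios that may be adjusted, again without naming covariates.

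For the ACLF cohort, the Sample size section takes control mortality from published data, "with a rate of 33.9% demonstrated in a study of 1343 hospitalised patients", and continues: "A 75% reduction in mortality in the intervention group generates a mortality rate of 8.5" per cent. It arrives at "a total sample size of 120 participants or 60 in each arm for the ACLF cohort". No mortality rate is planned for the decompensation cohort. The Recruitment section puts all participants in the intention-to-treat analysis. The article does not say how a death enters MELD or quality of life.

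**The concern.** There are two separate issues.

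**Precision.** When an outcome is defined against a measured baseline, a t-test on the change (or on the follow-up value) is a less efficient use of that baseline than a regression that includes it. The loss is avoidable and costs no data.

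**Deaths in the ACLF cohort.** A patient who has died has no MELD, CLDQ or EQ-5D value. If the programme reduces mortality as far as planned, many more controls than intervention patients will be missing for that reason, and those missing will tend to be the sicker ones. A two-sample test on observed scores would then compare groups that are no longer the randomised groups. A programme that saves lives could look neutral or worse on severity and quality of life.

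**Working it through.** **1. The plan's mortality rates and sample size.** Inputs from the Sample size section: p₁ = 0.339, p₂ = 0.085, two-sided alpha 0.05, power 80%, dropout 20%.
- Pooled two-proportion formula: n = [1.96·√(2·0.212·0.788) + 0.8416·√(0.2241 + 0.0778)]² / 0.254² = 39.5, so 40 per arm.
- With continuity correction: (39.45/4)·[1 + √(1 + 4/(39.45·0.254))]² = 47 per arm.
- With dropout: 47/0.8 = 58.75, so 59 per arm and 118 in total, against the stated 120. The figure reproduces, so these are the rates the plan was built on.

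**2. Precision from the baseline covariate.** ρ is the correlation between baseline and follow-up. The documents do not give it, so it is an assumption. With equal variances (follow-up variance = 1), the variance factors are: follow-up score 1, change score 2(1−ρ), ANCOVA 1−ρ². The ratio of ANCOVA to change score is (1−ρ²)/[2(1−ρ)] = (1+ρ)/2.

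| ρ | ANCOVA / change | ANCOVA / follow-up |
|---|---|---|
| 0.3 | 0.65 | 0.91 |
| 0.5 | 0.75 | 0.75 |
| 0.7 | 0.85 | 0.51 |
| 0.8 | 0.90 | 0.36 |

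At ρ of 0.5–0.7 the reduction against change scores is 25% to 15%.

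**3. Who can have a day-28 score (ACLF only).** Control: 60 × 0.339 = 20.3 deaths, 39.7 alive. Intervention: 60 × 0.085 = 5.1 deaths, 54.9 alive. With 48 per arm after 20% dropout: 31.7 vs 43.9. Deaths after day 28 are not given, so these counts are upper limits for weeks 6 and 12.

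**4. Possible shift on the day-28 level, with no true effect on the score.** Assume a normal score that correlates r with a normal liability to death. With c = Φ⁻¹(1−p), the mean score among survivors is −r·φ(c)/(1−p) SD.
- Control: c = 0.415, φ = 0.366, 0.366/0.661 = 0.554.
- Intervention: c = 1.372, φ = 0.156, 0.156/0.915 = 0.170.
- Difference: 0.384·r SD, so 0.12, 0.19 and 0.27 SD at r = 0.3, 0.5 and 0.7, with LivR Well appearing sicker.

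In 4,000 simulated trials with 60 per arm, a survivor t-test on the level rejected in about 8%, 15% and 29% at those correlations, and in about 5% at r = 0.

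**5. The same for change scores.** The shift becomes 0.384·(r₂₈ − r₀), where r₂₈ and r₀ are the correlations of the day-28 and baseline scores with death liability.
- r₂₈ = 0.5, r₀ = 0.3: 0.08 SD.
- r₂₈ = 0.7, r₀ = 0.3: 0.15 SD.
- r₂₈ = r₀ = 0.5: 0.00 SD.

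**6. ANCOVA does not remove the shift.** The shift is roughly 0.384·(r₂₈ − ρ·r₀). At an assumed ρ = 0.6 the three cases give 0.384·0.32 = 0.12, 0.384·0.52 = 0.20 and 0.384·0.20 = 0.08 SD. The precision fix and the handling of deaths are therefore separate decisions.

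**The case against.** The strongest reply is that this is a condensed article, and that the handling of deaths and the choice of covariates commonly sit in an analysis plan that is not shown. That stands for the deaths. A reader might infer that the plan restricts MELD and quality of life to survivors, but no section says so. What can be said is conditional: a test on observed scores would have that effect. An intention-to-treat statement alone does not supply a score after death. The reply does not cover the precision point, because the article names the tests.

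It is also fair to say that a test on change does use the baseline, so the plan does not discard it; the loss is one of efficiency. The 0.12–0.27 SD shift belongs to the day-28 level, whereas the outcome is set against baseline, and for change scores it can be near zero.

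A further objection is that ranking deaths worst alters the question. At the planned rates with no effect on the score, such a test rejects in about 69% of trials when score and death are unrelated, and in about 43% at a correlation of 0.5 (60 per arm). This is right, and it is why that analysis should be supportive and labelled as a combined measure, not replace the score comparison.

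Finally, a reader might extend the criticism to the primary analysis. The documents do not support that: an unadjusted chi-squared test is valid under 1:1 randomisation, and possibly adjusted Cox hazard ratios are planned as well.

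**Conclusion.** The point holds as an improvement to the analysis of the continuous secondary outcomes, not as an error that invalidates them. For MELD, CLDQ and EQ-5D, ANCOVA would cut variance by 15–25% against change scores, assuming a baseline correlation of 0.5–0.7.

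The concern about deaths is real but confined to the ACLF cohort, 120 of 440 patients. At the planned mortality, about 40 vs 55 patients could have a day-28 score. The resulting shift is up to 0.12–0.27 SD on the level, and smaller, possibly nil, on change. These sizes rest on assumed correlations and on a score effect of zero; a true benefit on the score could offset the shift. The planned rates say nothing about the decompensation cohort. Child-Pugh class is ordinal, so the sentence on continuous outcomes does not clearly cover it. Covariate adjustment of the primary tests is optional.

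**What to change.** 1. In Statistical analyses, replace the two-sample tests for MELD, CLDQ and EQ-5D with ANCOVA: follow-up value as outcome, treatment arm and baseline value of the same score as terms, reported with 95% confidence intervals.
2. For the ACLF cohort, state how deaths enter these scores. Keep the observed-score ANCOVA, with the number of deaths and of available scores per arm beside it. Add a pre-specified supportive rank analysis (Mann-Whitney, which the article already allows) with deaths ranked below all survivors. State that it measures survival and score together and is not evidence of an effect on the score alone.
3. Leave the primary chi-squared tests as they are, unless the sponsor wishes to add an adjusted estimate.

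The cost is wording only, as the baseline and follow-up values are already scheduled. The rule for deaths should be fixed before any outcome data are seen by arm, including at the interim analysis, because a rule chosen afterwards would carry little weight.

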#### Recruitment

Patients will be recruited from the following settings: (a) following an acute hospital admission, (b) directly from the emergency department if able to be discharged home or (c) from the complex liver care clinic if ACLF or decompensation develops. All patients will be assessed by a gastroenterologist and allied health clinicians prior to recruitment. A research assistant or Pharmacist Informatician will provide eligible patients with a Participant Information and Consent Form (PICF) (Appendix 4) and consent will be obtained by a sub-investigator. Patients will be reviewed and admitted to the programme on the day of enrolment. All patients receiving LivR Well will also be onboarded to a mobile application and provided with the requisite hardware and software. Participants will be discontinued from the trial if consent is withdrawn, or if a serious adverse event (as defined on page 9) or death occurs. All participants will be included in the intention-to-treat analysis. If patients are admitted to the hospital after enrolment but before completion, the 28-day programme can be re-started on discharge if the patient still meets eligibility criteria and at the discretion of the treating team.

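### The subgroup analysis by referral source is presented as addressing earlier discharge of LivR Well in-patients, but it cannot remove that bias, which lies between the arms within the in-patient stratum

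*Protocol article*

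**What the plan says.** The Statistical analyses section plans three exploratory subgroup analyses. The first, by source of referral, has a stated purpose: it is "conducted to address bias created following randomisation whereby in-patients in the intervention arm may be discharged home earlier" than control in-patients, because home visits make early discharge feel safe. The section adds: "This subgroup analysis will account for differences between those admitted from in-patient admission compared to the emergency department or the ambulatory liver clinic".

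Other parts of the protocol show how discharge timing could come to depend on arm:

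- Screening and randomisation: participants are "informed of their allocation by the CLD nurse specialist prior to discharge or within 24 hours of obtaining informed consent".
- Discussion: "The trial is unblinded by nature, which may influence decisions such as referral for liver transplantation, re-admission to and discharge from hospital".
- Statistical analyses: readmission is counted from discharge ("30-day readmission from the date of hospital discharge will be undertaken on an intention-to-treat basis"), whereas for death "A 28-day mortality rate will be calculated from the date of randomisation".
- Outcomes: 30-day readmission is the primary outcome of the hepatic decompensation cohort.

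The Discussion calls the subgroups exploratory, concedes potential for bias and difficult interpretation, and expects them to lack power.

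**The concern.** The problem named and the remedy offered do not match. The problem is that, among in-patients, one arm may go home sooner than the other once allocation is known. The remedy compares in-patients with patients referred from the emergency department or clinic. A baseline factor that randomisation balances in expectation cannot correct a difference between arms that arises later and inside one of its levels.

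This matters mainly for readmission. For in-patients told their allocation before leaving, the 30-day clock starts at an event that allocation may already have moved, and the arms may start it at different stages of recovery. The sponsor predicts this, and no analysis in the protocol removes it. A report that follows the Statistical analyses wording could present the matter as dealt with while the in-patient readmission estimate still carries it.

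**Working it through.** The protocol gives no figure for this bias, so there is nothing to reproduce. The check has a structural part, which needs no assumed values, and an illustration of size, which does.

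**1. Where the bias sits.** Let *s* be the in-patient share and *b* the spurious risk difference (LivR Well minus control) caused by earlier discharge among in-patients. The protocol gives neither. Allocation is 1:1 ("randomised in a 1:1 ratio to either the LivR Well programme or to complex care liver clinic").

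- In-patient stratum: bias = *b*.
- Emergency-department and clinic strata: bias = 0. These patients have no in-patient stay to shorten; for example, the former are recruited "directly from the emergency department if able to be discharged home".
- Crude overall estimate: bias = *s* × *b*.
- Referral-stratified overall estimate: *s* × *b* + (1 − *s*) × 0 = *s* × *b*, the same as the crude one.

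A simulation of 2,000,000 patients with no true effect, *s* = 0.7 and *b* = 5 points gave:

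| Estimate | Bias (points) | Expected |
|---|---|---|
| In-patient | 4.97 | 5.0 |
| Emergency department/clinic | 0.12 | 0 (rest is noise) |
| Crude overall | 3.52 | 0.7 × 5 = 3.5 |
| Referral-stratified overall | 3.51 | 3.5 |

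Stratifying changes nothing overall, and the in-patient subgroup shows the bias undiluted.

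**2. What a difference between strata would show.** If the true effects are *d*₁ (in-patients) and *d*₂ (others), the observed contrast between strata is (*d*₁ + *b*) − *d*₂. The data identify only the sum (*d*₁ − *d*₂) + *b*. A bias and a true difference in effect cannot be separated.

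**3. Illustrative size, readmission counted from discharge as written.** Assumptions: constant hazard *h*, 30-day in-patient risk of 32% without the bias, and a hazard 10-30% higher after earlier discharge. The 32% is back-calculated. Against the stated 17%, with 80% power and two-sided 5% alpha, it needs 128 per arm; 128/0.8 = 160, the stated number per arm. With a continuity correction, 33% gives 316 in total, also close to 320. The protocol states no single control rate.

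- *h* = −ln(0.68)/30 = 0.01286 per day.
- Risk with hazard multiplied by *k*: 1 − 0.68^*k*.

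| *k* | Risk | Added (*b*) | Overall if *s* = 0.5 | Overall if *s* = 0.9 |
|---|---|---|---|---|
| 1.1 | 34.6% | 2.6 points | 1.3 | 2.3 |
| 1.2 | 37.0% | 5.0 points | 2.5 | 4.5 |
| 1.3 | 39.4% | 7.4 points | 3.7 | 6.7 |

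If LivR Well in-patients would otherwise have the planned 17%, the same hazards add less: 1 − 0.83^*k* gives 18.5%, 20.0% and 21.5%, or 1.5, 3.0 and 4.5 points. The effect implied by 320 patients is about 32 − 17 = 15 points. Every shift raises LivR Well readmission.

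**The case against.** The strongest reply is that the protocol claims less than one sentence suggests. It labels the subgroup exploratory. The Discussion admits possible bias and low power, lists discharge among the decisions open to influence, says such influence will be hard to address and promises to discuss it. The emergency-department and clinic strata do give an estimate free of this mechanism. All of this stands, and it lowers the weight of the point. It does not withdraw the stated purpose in the Statistical analyses section, and that purpose is wrong.

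It can also be argued that earlier discharge made possible by home visits is part of the effect of assignment, not a bias. That fits 28-day mortality counted from randomisation, so the point is not pressed there. For readmission the sponsor itself uses the word bias and offers this analysis against it. If earlier discharge is part of the effect, the rationale is mistaken for another reason.

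A reader might also infer more than the protocol supports:

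- *That earlier discharge gives LivR Well patients more days at risk.* This would hold only if readmission were counted from randomisation. The protocol counts it from discharge, so both arms have 30 days.
- *That the gap between arms is known to be several days.* No gap is given. The Processes section places enrolment at discharge from the acute admission, so it may be short.
- *That the result could be falsely positive.* In the scenario shown, the shift works against LivR Well.
- *That the subgroup is worthless.* It is a weak check, not a correction.

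**Conclusion.** The point holds in a limited form. The referral-source subgroup cannot do what the Statistical analyses section says it is for: the in-patient estimate keeps the whole bias, and the overall estimate is the same with or without stratification. That conclusion is structural and does not depend on any assumed value.

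The size is not known. The 2.6-7.4 points among in-patients rest on an assumed 32% risk, a constant hazard and an assumed 10-30% rise in hazard; they fall to 1.5-4.5 points from a 17% risk, and shrink further overall in proportion to the in-patient share. The likely consequence is a masked benefit. The planned primary comparison can still be made, so this is a correction that should be made and does not invalidate the trial.

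**What to change.** 1. In Statistical analyses, delete the statements that the referral-source subgroup is conducted to address this bias and will account for the differences. Describe it as an exploratory look at effect modification.
2. Report days from randomisation to index discharge by arm among in-patients. This shows directly whether the predicted difference occurred and how large it was.
3. Pre-specify, as a sensitivity analysis for the decompensation primary, days alive and out of hospital to day 30 from randomisation. Both arms then share a time origin, and index and readmission days count alike. It treats earlier discharge as part of the effect of assignment, so it complements the readmission rate and does not estimate readmission with discharge timing held equal.

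The cost is a little more analysis and the extraction of index and readmission discharge dates from hospital records; Data collection lists hospital admissions and death but does not name these dates.

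For in-patients, allocation could also be released only after the discharge decision is recorded. That is optional. Recruitment opened in January 2022, so it would change conduct for later participants only and leave less time to arrange home visits.
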